## 2. Materials and Methods

### 2.1. Study Design

The GAITFAST study (gait recovery in patients after acute ischemic stroke) was designed as an investigator-initiated, academic, single-blind, single-center, prospective, randomized clinical trial with two parallel groups and a primary endpoint of gait speed recovery up to 6 months after ischemic stroke. The protocol of the proposed GAITFAST trial is registered on ClinicalTrials.gov with identifier NCT04824482. The trial design follows the Recommendations for Interventional Trials (SPIRIT), the TIDieR checklist was used in conjunction with the SPIRIT. This study will be performed at the University Hospital Olomouc, Czech Republic. All participants will be enrolled at the Comprehensive Stroke Centre, and the neurorehabilitation interventions, including assisted gait training (RTGT or TTGT), will be performed at the Department of Rehabilitation.

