#### 2.6.1. Primary Outcome

Walking speed is defined as a primary outcome in this study and is the most used outcome measure of walking ability in locomotor rehabilitation. Walking speed has been shown to be a predictor of independence, the functional level at home and within the community, and quality of life [25]. Gait speed will be evaluated before the beginning of inpatient RHB, after two weeks (at the end of inpatient RHB), and during follow-up (three and six months after stroke onset). Gait speed will be measured using the 10-meter walking test. The subject will be asked to walk a distance of 10 m at his/her comfortable speed. The time will be measured for the distance of the middle six meters, which will reflect walking acceleration and deceleration. If the physical assistance of another person (to prevent a fall or collapsing) is needed for a patient to complete the test, the level of assistance will be documented. If total assistance or assistance for limb swing or forward propulsion is required, a walking speed of 0 m/s will be documented [26]. The usage of any assistive device and/or bracing (that patients use for walking and are needed to complete the test) will also be documented. Based on the gait speed, walking may be classified as household (<0.4 m.s^−1^), limited community (0.4 to 0.8 m.s^−1^), or full community ambulation (>0.8 m.s^−1^) [20].

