### 2.7. Sample Size

Based on an analysis of our pilot data concerning the gait velocity (primary outcome), 120 participants (60 in each group) are anticipated to be enrolled in this study. This number of participants would provide 85% power (α level 5%) to detect a difference of 0.16 m/s in the 10 MWT (with respect to a missing data rate of 15% and an expected 10% drop in the follow-ups) between groups after intensive rehabilitation with add-on intervention. The gait speed difference of over 0.16 m/s was previously defined as the minimal clinically important difference in gait speed in subacute stroke patients [46].

For the multimodal magnetic resonance imaging (MRI), including functional MRI (fMRI), we have estimated that a sample size of 50 participants (25 in each group) will suffice to find significant correlations of MRI outcomes with gait recovery. This is based on previous studies of fMRI and gait recovery in similar clinical cohorts [29,32]. We will perform multimodal MRI in half of the randomly selected enrolled IS patients (1:2 randomization), i.e., in 60 participants, to allow for a common drop-out of examined patients with MR images of poor or insufficient quality. As we do not have sufficient information to estimate the variance in the outcomes, we plan to calculate the definitive effect sizes based on the interim analysis of the first 30 subjects measured within all four visits (visit 1–visit 4).

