### 2.10. Statistical Analysis

For the statistical analysis of all tested clinical parameters, gait movement pattern parameters, and extracted imaging parameters, the distribution of the data will first be explored. If normally distributed, a two-factor mixed-model ANOVA will explore the differences between the groups and time points. If not normally distributed, Friedman tests will be used to explore the differences between time points (visits 1–4) within each group and Mann–Whitney U tests will be used to explore the differences between both groups (RTGT and TTGT).

The statistical analysis of fMRI data will include standard preprocessing with subsequent general linear model fitting and a group-wise analysis in the Montreal Neurological Institute (MNI) 152 standard space after the nonlinear normalization of the individual structural MRI data [49]. Significant group effects will be evaluated using an analysis of covariance (ANCOVA) with group, visit, and age as covariates. An atlas-based region of interest (ROI) analysis will be used to evaluate the amplitude and volume of the primary sensorimotor and premotor activations and the laterality index (ipsilesional − contralesional/ipsilesional + contralesional), which are the main secondary outcome measures of the fMRI analysis. Since the functional study design and paradigm partly follow the study of Boyne et al. [32], the choice of regressors and contrasts for the statistical analysis of the corresponding data will likewise follow that study. Structural data (DWI and T1-weighted) will be evaluated in separate pipelines to extract the following parameters from anatomically defined ROIs: regional cortical thickness; fractional anisotropy (FA); and axial, radial, and mean diffusivity (AD, RD, and MD), respectively. Alternative DWI analysis models may include, e.g., FD/FDC or NODDI. The quantitative parameters derived from functional and structural imaging will be included in an extended factor analysis of the global predictors of gait recovery.

With respect to the type of missing variable, the appropriate imputation (e.g., single imputation, multiple imputation, etc.) might be performed if needed [50].

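### Gait speed is the primary outcome, but no primary visit or contrast is named, the test is chosen from the data, and the 85% power refers to a comparison that the analysis section does not identify

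*Protocol article*

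**What the plan says.** Section 2.1 of the protocol article gives the trial "a primary endpoint of gait speed recovery up to 6 months after ischemic stroke", and the abstract says the same. Section 2.6.1 measures gait speed by the 10-metre walking test before the programme, at its end, and at three and six months. None of these is called primary. The same section says that for patients who need total assistance, or help with limb swing or propulsion, "a walking speed of 0 m/s will be documented".

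Section 2.7 justifies 120 participants from pilot data: "This number of participants would provide 85% power (α level 5%) to detect a difference of 0.16 m/s in the 10 MWT". The difference is one "between groups after intensive rehabilitation with add-on intervention", after allowance for 15% missing data and 10% loss to follow-up. No SD is given. The description reads as visit 2, although no visit number appears.

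Section 2.10 has no separate primary analysis. All clinical parameters follow one rule, applied once the distribution has been explored: "If normally distributed, a two-factor mixed-model ANOVA will explore the differences between the groups and time points". If the data are not normal, "Friedman tests will be used to explore the differences between time points" within each group, and Mann–Whitney U tests compare the two groups. ANCOVA appears only for fMRI, with group, visit and age. Section 2.10 also lets the interim data on 30 participants guide the final methods.

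**The concern.** Three statements should describe one comparison: the endpoint, the powered difference and the primary test. Here the endpoint spans three post-baseline visits, the power belongs to one of them, and the analysis section names neither a visit nor a contrast.

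The tests it does name are not interchangeable:

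- **ANOVA group main effect.** It averages over all four visits, including visit 1, before any treatment has been given.
- **ANOVA group × time interaction.** It does reflect change from baseline, but as a 3-df omnibus test. It can be significant for any pattern of divergence and does not estimate the 0.16 m/s contrast.
- **Friedman tests.** Run within each arm, they show whether patients change over time. They do not compare RTGT with TTGT.
- **Mann–Whitney tests.** They do compare the arms, but as written with no visit named and no baseline adjustment.

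The observed distribution decides which set applies. A positive report could therefore rest on any of several tests or visits, and a reader could not tie it to one prespecified hypothesis.

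**Working it through.** **Inputs from section 2.7:** difference δ = 0.16 m/s, α = 5% (taken as two-sided), power 85%, 60 per arm, 15% missing data, 10% loss to follow-up. **Assumed, because the article gives neither:** the SD, and the correlation ρ between visits (equal SDs and equal correlations, ρ = 0.4–0.7).

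**1. The plan's own figure.** For one two-sample contrast, SD = δ·√(n/2) / (1.960 + 1.036).

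- n = 60 (no losses): 0.16 × 5.477 / 2.996 = 0.292 m/s
- n = 51 (15% loss): 0.270 m/s
- n = 60 × 0.85 × 0.90 = 45.9: 0.256 m/s
- n = 45 (25% loss in total): 0.253 m/s

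So 120 is consistent with a single two-group comparison, but it cannot be verified without the SD. Below I use SD 0.256 and n = 46. The standard error of a single-visit difference is then 0.256 × √(2/46) = 0.0534.

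**2. Single visit, unadjusted.** 0.16/0.0534 = 2.997; power = Φ(2.997 − 1.96) = 85%. A Mann–Whitney test at that visit, with relative efficiency 0.955 under normality: Φ(2.997 × √0.955 − 1.96) = 83%.

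**3. Same visit, ANCOVA on visit 1 gait speed.** The standard error is multiplied by √(1 − ρ²). At ρ = 0.4: 2.997/0.917 = 3.270, power 90%. At ρ = 0.7: 2.997/0.714 = 4.197, power 99%.

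**4. ANOVA group main effect.** The standard error is 0.0534 × √((1 + 3ρ)/4), that is 0.0396 at ρ = 0.4 and 0.0470 at ρ = 0.7.

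- Effect at visits 2, 3 and 4: mean difference 3 × 0.16/4 = 0.12; power 86% falling to 72%.
- Effect at visit 2 only: mean difference 0.16/4 = 0.04; power 17% falling to 13%.

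**5. ANOVA interaction.** Noncentral F with 3 and 3 × (92 − 2) = 270 df, and noncentrality (n/2)·Σ(δₜ − δ̄)² / [SD²(1 − ρ)]. For an effect at all three later visits, or at visit 2 only, Σ(δₜ − δ̄)² = 0.75 × 0.16² = 0.0192. At ρ = 0.4 this gives 23 × 0.0192 / (0.0655 × 0.6) = 11.2, power 81%. At ρ = 0.7 it gives 22.5, power 99%. If the effect fades (0.16, 0.08, 0.04), power is 66%–94%.

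**6. Multiplicity, if any visit could count.** Three two-sided 5% tests with common correlation ρ, by multivariate-normal simulation, have a family-wise error of about 13% at ρ = 0.4, 11% at ρ = 0.7 and 10% at ρ = 0.8.

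| Test (effect at visit 2 only) | Power, ρ = 0.4 to 0.7 |
|---|---|
| ANOVA group main effect | 17% to 13% |
| ANOVA interaction, 3 df | 81% to 99% |
| Mann–Whitney at visit 2 | about 83% |
| Unadjusted difference at visit 2 | 85% |
| ANCOVA at visit 2 | 90% to 99% |

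**The case against.** The strongest reply is that the article condenses a fuller plan, that an unadjusted randomized comparison is valid, and that covariates and multiplicity are commonly left to the SAP. Much of this stands. Lack of baseline adjustment costs precision and leaves chance imbalance uncorrected; it does not bias the comparison or make 120 the wrong number. Silence on covariance structure is no fault either. The reply does not cover what the article does fix: an endpoint and a powered contrast that differ, and a data-selected rule for the primary outcome.

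Four stronger readings are tempting, and the document does not support them:

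- *Baseline gait speed is thrown away.* Not in the ANOVA branch: visit 1 is a time level there, so the interaction uses it. Only the Mann–Whitney route, as written, lacks it.
- *The 85% belongs to none of the named tests.* Too strong. It lies inside the interaction's range, a Mann–Whitney test at visit 2 comes close, and the main effect reaches 86% for a sustained effect at ρ = 0.4. What can be said is that the article does not identify the test.
- *Patients with a missed visit are lost.* Not established. Section 2.10 allows imputation, and a mixed model may be fitted by likelihood to incomplete data. Section 2.7 already allows for losses.
- *The zero coding makes the non-normal branch likely.* Section 2.2.1 requires FAC 1–3 at enrolment, and no share of zeros is given. A cluster at zero is possible, but its size is unknown.

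The family-wise error is also conditional: section 2.10 does not say that one significant visit would count as success.

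**Conclusion.** The concern holds in this form: no primary visit or contrast is named, the endpoint and the power statement describe different things, and the primary test depends on the observed distribution. For an effect confined to visit 2, the time point that section 2.7 appears to power, the ANOVA's own two between-group tests range from 13% to 99% power. The 85% can therefore be attached to a particular analysis only by guessing. ANCOVA at the same visit would give 90%–99% with the same patients, which is an improvement in precision and not the correction of an invalid test. The open choice of visit could raise type I error to about 11%–13% if any visit were allowed to count.

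The mismatch itself needs no assumption; it is in the text. The power figures rest on a back-solved SD, 46 evaluable per arm, two-sided testing and an assumed common correlation, and show scale only. This should be settled before outcome data, including the interim data, are examined.

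**What to change.** - Name one primary visit and one between-group contrast: visit 2 if section 2.7 states the intention, visit 4 if section 2.1 does. Make the other visits secondary.
- State the SD for that visit, its source, and the power it gives.
- Analyse the contrast with a prespecified model adjusted for visit 1 gait speed: ANCOVA at that visit, or a mixed model for visits 2–4 with group, visit, group × visit and visit 1 gait speed. Keep this model whatever a distribution check shows.
- Use a rank-based or bootstrap analysis as a sensitivity analysis, not as a replacement selected from the data.
- Do not present within-arm Friedman tests as evidence of a difference between treatments.

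The cost is mostly wording, with no extra measurements. The other visits become formally secondary. If visit 4 is chosen, the stated power must be restated with a six-month SD that the article does not give, and the sample size might then need another look.

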## 1. Introduction

After ischemic stroke (IS), the majority of people have some walking disabilities. Approximately 30% of IS patients are unable to walk without assistance six months after a stroke [1], and more than 60% of individuals who achieve independent ambulation after IS still walk at speeds insufficient to function effectively in the community [2]. Walking is one of the most important activities of daily living (ADL), and restoring gait function has become a critical goal of poststroke rehabilitation [2,3].

Early neurorehabilitation interventions seem to be critical to enhance neural plasticity and brain repair processes and to potentiate physiological motor behavioral restitution (i.e., restoring the physiological movement pattern) rather than mere compensation (adaptive mechanisms to utilize the residual capacity to accomplish a motor task) [3,4]. Functional brain imaging provides the possibility to describe neuroplastic brain adaptations related to motor recovery [5] and rehabilitation [6].

Current neurorehabilitation approaches mostly focus on task-specific training and intensive and repetitive exercise [7,8,9,10,11] with increases in both the therapy dosage and intensity [3,11]. Additional (add-on) physical rehabilitation, as compared to usual care or a control intervention, demonstrated the potential to further improve motor function, standing balance, or walking speed [11]. As the vast majority of poststroke patients experience some recovery, mostly occurring in the first weeks after stroke [4,12,13], the optimal time window to begin rehabilitation seems to be the early subacute stage (within the first weeks after stroke onset [14]).

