### 2.5. Study Protocol

All enrolled participants will be examined by evaluators that will be blinded to the group allocation. The assessments will be realized by certified neurologists, rehabilitation physicians, physiotherapists, and biomedical engineers with respect to their specialization at four assessment timepoints. Clinical visits will occur as follows:

Visit 0 (T0): enrolment 5–10 days after onset of qualifying IS at the Comprehensive Stroke Centre.

Visit 1 (T1) (3–5 days after V0): assessment before the initiation of an intensive rehabilitation program including assisted gait training (RTGT or TTGT) at the Department of Rehabilitation.

Visit 2 (T2) (14 ± 7 days after visit 1 and 1 month after visit 0): assessment at the end of the intensive rehabilitation program including gait training at the Department of Rehabilitation.

Visit 3 (T3): assessment 12 ± 1 weeks after visit 0 (3 months after visit 0).

Visit 4 (T4): assessment 24 ± 2 weeks after visit 0 (6 months after visit 0).

Scheduled outpatient visits in the GAITFAST trial will be performed by a neurologist at the Department of Neurology (visit 1–visit 4), a rehabilitation physician, a physiotherapist, and a biomedical engineer at the Kinesiology Laboratory at the Department of Rehabilitation (visit 1–visit 4). Multimodal MRI data will be acquired on a 3T scanner (Siemens Magnetom Vida, Erlangen, Germany) at the Department of Radiology. Scanning will be supervised by a member of the Functional Magnetic Resonance Imaging Laboratory (visit 1–visit 4). The duration of patient participation will be 6 months (Table 1).

Each visit will include an assessment to evaluate gait speed, gait dependency, neurological impairment, sensorimotor function, and gait biomechanics and a multimodal MRI of the brain. The outcome variables and study flow are presented in more detail in Table 2.

As data accumulate, the validity and the integrity of the trial will be subjected to an interim analysis after the first 30 participants have been assessed at all four assessment timepoints. With respect to the results of the interim analysis, the study design (such as the sample size, allocation ratio, or eligibility criteria) might be adaptively modified.

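### Section 2.10 selects a two-factor mixed ANOVA over four visits on normality alone; sphericity is unlikely, and an uncorrected group-by-visit test could run at about 5–10% instead of 5%

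*Protocol article*

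**What the plan says.** Section 2.10 sets one rule for the clinical, gait-pattern and extracted imaging parameters. The distribution is explored first. Then: "If normally distributed, a two-factor mixed-model ANOVA will explore the differences between the groups and time points". Otherwise Friedman and Mann–Whitney tests are used. Sphericity, a covariance structure and an epsilon correction are not mentioned, and nothing says they will be left out.

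Section 2.5 places T1 3–5 days after visit 0 and T2 about two weeks after T1. T3 is an "assessment 12 ± 1 weeks after visit 0 (3 months after visit 0"), and T4 comes at 24 weeks. Table 1 counts the last two from T1 instead. The Introduction describes recovery as "mostly occurring in the first weeks after stroke". Under section 2.2.1 all patients enter as dependent walkers (FAC 1–3). Under section 2.6.1 a patient who needs total assistance, or help with limb swing or propulsion, is scored 0 m/s.

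Section 2.7 says 120 patients "would provide 85% power (α level 5%) to detect a difference of 0.16 m/s in the 10 MWT" "between groups after intensive rehabilitation with add-on intervention", allowing for 15% missing data and a 10% drop in follow-up. It gives no SD or between-visit correlation. Section 2.10 adds that the interim analysis of 30 complete patients will guide the final statistical methods.

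**The concern.** A classical two-factor (group, visit) mixed ANOVA pools one within-patient error over all visits. The group-by-visit F test keeps its nominal level only if the differences between all pairs of visits are equally variable. Normal data can violate this badly, so a check of normality gives no protection.

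Several features of this trial point to unequal variances. The visits are unevenly spaced. Patients start near the floor of the scale, so their spread can widen as walking returns. The trial also looks for predictors of gait recovery, which presupposes that patients recover at different rates.

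The group-by-visit term is the part of the ANOVA that compares the course of recovery between arms. The group main effect uses between-patient error and is not affected. Follow-up contrasts that use the pooled error would also carry the wrong precision at individual visits. The same rule applies to every outcome that takes the ANOVA branch.

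**Working it through.** **1. The plan's own figure.** Per arm, n = 2(z₀.₉₇₅ + z₀.₈₅)² SD² / 0.16², so SD = 0.16 × √(n / (2 × (1.960 + 1.036)²)). Two-sided testing is assumed, because the article does not state it. With 60 per arm the SD is 0.29 m/s. With 45 per arm (60 × 0.75) it is 0.25 m/s; compounding the losses gives 60 × 0.85 × 0.90 = 45.9, about 46. The 120 cannot be confirmed, because no SD is given. The SD would not settle the present point anyway: the type I error of the F test depends only on the correlations and on the relative SDs across visits.

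**2. Visit gaps.** T1–T2 is about 2 weeks. With T1 at about 4 days (0.6 weeks) and T2 at about 2.6 weeks after visit 0, T2–T3 is 12 − 2.6 = 9.4 weeks. It is about 7.7 weeks if T2 falls one month after visit 0, and 10–11 weeks under Table 1. T3–T4 is about 12 weeks.

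**3. Group-by-visit test without correction.** The test was simulated with no group effect: two arms, visits at weeks 0, 2, 12 and 24, and 100,000 runs per case. All covariances are assumptions. Epsilon is the Greenhouse-Geisser measure: 1 means sphericity holds, and 1/3 is the worst case with four visits.

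| Assumed covariance | Epsilon | Rejection at nominal 5% (60 per arm) |
|---|---|---|
| Compound symmetry | 1.00 | 5.0% |
| Constant correlation 0.7–0.8, SD growing over visits | 0.85–0.96 | 5.2–5.9% |
| AR(1) by visit number, 0.5–0.85 | 0.70–0.86 | 5.7–6.8% |
| Correlation decaying with time, 0.5–0.9 per 12 weeks | 0.57–0.66 | 7.1–8.0% |
| Same at 0.7–0.8, with 10% measurement noise | 0.74–0.77 | about 6.5% |
| Random intercept plus random slope, small to large | 0.95–0.42 | 5.2–9.7% |
| Worst case | 0.33 | 10.8% |

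With 45 per arm the results move by no more than about 0.3 points. With the Greenhouse-Geisser correction the rate is 4.7–5.1% throughout.

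**4. Contrasts that use the pooled error.** The ratio of pooled to correct standard error is √(mean variance of the six pairwise differences / variance of the difference in question). The actual test size is about 2[1 − Φ(1.96 × ratio)].

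- *Correlation 0.7 per 12 weeks, constant SD.* The difference variances are proportional to 1 − ρ. For T1–T2, T1–T3, T1–T4, T2–T3, T2–T4 and T3–T4 these are 0.058, 0.300, 0.510, 0.257, 0.480 and 0.300, with mean 0.317. T1–T4: √(0.317/0.510) = 0.79, so the interval is 21% too narrow and the test runs at about 12%. T1–T2: √(0.317/0.058) = 2.3, so the interval is far too wide and the test hardly ever rejects.
- *Patients differing mainly in early recovery* (independent increments with variances 0.04, 0.01 and 0.005). In the same order, the difference variances are 0.040, 0.050, 0.055, 0.010, 0.015 and 0.005, with mean 0.175/6 = 0.029. T1–T2: √(0.029/0.040) = 0.85, now too narrow. T1–T4: √(0.029/0.055) = 0.73, also too narrow.

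Across the non-spherical structures simulated in step 3, the pooled-error test of T1–T4 change ran at about 5–19% and that of T1–T2 change at about 0–4%. The second example shows that the T1–T2 direction can reverse.

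**The case against.** The strongest reply is that the article never says the F test will be uncorrected, or that one pooled error will serve every contrast. The term used for the ANOVA excludes neither an epsilon correction nor a modelled covariance, and an analysis plan that is not shown may specify either. This stands, and it makes the whole point conditional. What remains is that the article does fix a selection rule, and normality is not the condition that protects this test.

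Four stronger readings are tempting, and the document does not support them:

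- *The schedule rules sphericity out.* It does not. A random-intercept structure satisfies sphericity at any spacing, and the Introduction describes when recovery happens, not its variances.
- *The test runs at 6–9%.* No covariance is given, so no single figure or narrow band can be attributed to this trial.
- *The stated 5% and 85% are breached for the interaction or for T1–T2 change.* Both figures belong to the between-group comparison after rehabilitation in section 2.7. The interaction is not named as the powered or primary test.
- *The T1–T2 interval must be too wide.* The second example in the working shows the opposite.

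The floor argument also has a limit. A pronounced pile-up at 0 m/s would probably fail the normality check and send gait speed to the rank tests.

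**Conclusion.** The concern holds in conditional form. Sphericity is unlikely here, and the rule in section 2.10 does not guard against its failure. If the ANOVA is run without correction, the group-by-visit test has a type I error of about 5–10% at a nominal 5%. It is exactly nominal under compound symmetry and bounded at about 10.8%. Contrasts from the pooled error would generally overstate precision for T1–T4; for T1–T2 the error could go either way. These figures rest on assumed covariances, visits at weeks 0, 2, 12 and 24, and 45–60 analysed per arm. This is a modest weakness with a cheap remedy. It does not show that the planned analysis is invalid.

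**What to change.** In section 2.10, replace the two-factor mixed ANOVA with a group-by-visit repeated-measures model with unstructured covariance, and take the arm contrasts at each visit from it. The model is valid with or without sphericity. It also keeps patients with incomplete visits, whom a classical ANOVA drops unless their data are imputed. That matters with 15% missing data and 10% follow-up loss expected, and with imputation left optional. If the ANOVA is kept, state that p-values will be Greenhouse-Geisser corrected and that each contrast will use its own error term.

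The cost is about one sentence and slightly less favourable omnibus p-values. Four visits need ten covariance parameters (4 variances and 6 covariances), which about 90 patients can support. Make the change before the 30-patient interim analysis. That analysis is to guide the final methods, and the principal investigator will see its results, so a later choice of error structure could be informed by the data.

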Specific brain structures with possible impacts on gait recovery in IS patients will be identified using functional magnetic resonance imaging (fMRI) during simple lower limb movements, gait imagery, and gait observation as well as using diffusion-weighted imaging (DWI) and surface-based morphometry. The functional MRI activation magnitude, calculated as the difference in the BOLD signal between task and rest, will be assessed within predefined gait-related brain regions of interest (ROIs), i.e., the sensorimotor cortex, premotor cortex, supplementary motor area, brainstem, and cerebellum. Changes in these ROI parameters over time will be statistically tested within the group, and the regional post-training minus pretraining difference in each group will be submitted to a between-group analysis. Gait recovery after treadmill exercise has been associated with increased task-related activation in the posterior cerebellum and brainstem [28] as well as in the primary sensorimotor cortices and basal ganglia [29]. Moreover, the task-related activation volume in the ipsilesional primary sensorimotor foot representation has been identified as an independent baseline predictor of gait recovery [30]. However, simple leg movements may not be sufficiently representative of a more complex motor behavior such as gait. As it is impossible to directly measure gait-related brain activation in fMRI, gait imagery has been employed as a substitute for real movements in healthy subjects [31] as well as stroke patients with gait impairment [32]. Beyond fMRI, other potential imaging biomarkers include white matter integrity, assessed using diffusion-weighted imaging (DWI), and surface-based morphometry based on structural imaging [33]. So far, according to systematic reviews, evidence for biomarkers based on fMRI, DWI, and structural MRI data remains inconclusive, mostly due to methodological limitations [16].

-Neurological impairment

The National Institute of Health Stroke Scale (NIHSS) represents the most widely used rating scale to evaluate neurological impairment after IS [34]. The NIHSS includes items on consciousness, language, movement, sensation, ataxia, eye movement, the visual field, and others. The scores range from 0 to 42, with higher scores indicating more severe neurological deficits.

-Sensorimotor impairment

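### The fMRI group test in section 2.10, read literally, averages the pre-training scan into the group effect, lists no participant term, and conflicts with two other fMRI tests in the protocol

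*Protocol article*

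**What the plan says.** The protocol article describes the between-arm fMRI comparison in three ways.

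- **Section 2.10, fMRI paragraph.** After preprocessing, general linear model fitting and group-wise analysis in standard space: "Significant group effects will be evaluated using an analysis of covariance (ANCOVA) with group, visit, and age as covariates". No participant term and no group-by-visit term is listed.
- **Section 2.10, opening paragraph.** The general method is introduced with "For the statistical analysis of all tested clinical parameters, gait movement pattern parameters, and extracted imaging parameters". It continues: "If normally distributed, a two-factor mixed-model ANOVA will explore the differences between the groups and time points". Friedman and Mann–Whitney tests are the fallback if the data are not normal.
- **Section 2.6.2, brain activity.** For activation in predefined regions of interest (ROIs), "the regional post-training minus pretraining difference in each group will be submitted to a between-group analysis".

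Section 2.10 adds, with reference to a cited study whose design and paradigm the trial partly follows, that "the choice of regressors and contrasts for the statistical analysis of the corresponding data will likewise follow that study".

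On the number of scans, section 2.5 says "Scanning will be supervised by a member of the Functional Magnetic Resonance Imaging Laboratory (visit 1–visit 4"), and it places visit 1 before the intensive rehabilitation programme starts. Section 2.7 plans MRI in half of the enrolled patients, "i.e., in 60 participants, to allow for a common drop-out of examined patients with MR images of poor or insufficient quality", and regards 50 (25 per arm) as enough.

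**The concern.** Because visit is a covariate, scans from more than one visit enter the same model. Two separate problems follow if the sentence is carried out as it stands.

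The first is the contrast. A group main effect without an interaction is the between-arm difference averaged over all visits, including the one before any training. It is not the effect of training.

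The second is the error term. Scans of the same person are correlated. A model with only group, visit and age has one residual variance, so it tests a between-participant factor as if every scan came from a different person.

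fMRI activation is a listed secondary outcome and underlies the trial's aim of explaining the mechanism of gait recovery. There are also three candidate tests with no stated order. Section 2.10 lets the interim analysis of 30 participants guide the final statistical methods and gives the principal investigator access to those results, so the choice among the three could be made after seeing data.

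**Working it through.** **Inputs from the protocol.** Four scans per participant (2.5). 60 MRI participants planned and 50 (25 per arm) needed (2.7). Model terms group, visit and age (2.10). The protocol states no false-positive rate for fMRI, so there is no figure of its own to reproduce.

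**Assumed inputs.** Two-sided 5% for fMRI (2.7 gives a 5% level for the primary outcome only). ICC between scans of one person 0.1 to 0.9, with 0.3 to 0.7 as the middle range. Equal correlation between all pairs of visits. All four scans present and pooled.

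**Step 1: what the group coefficient estimates.** With complete data and no interaction, it is the mean of the four visit-specific between-arm differences, each with weight 1/4. If training produces the same effect d at visits 2, 3 and 4 and none at visit 1:

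(0 + d + d + d) / 4 = 0.75 d

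A chance difference b at visit 1 adds b/4 through that scan alone, and more to the extent that it persists at later visits. This step needs no ICC. It also holds if a participant term is added but the contrast is left unchanged. The figure of 75% does rest on an equal effect at visits 2 to 4.

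**Step 2: type I error without a participant term.** The true variance of the group coefficient exceeds the modelled one by the design effect 1 + (4 − 1) × ICC. The actual error at a nominal two-sided 5% is therefore

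2 × [1 − Φ(1.96 / √(1 + 3 × ICC))]

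| Assumed ICC | Design effect | Error by formula | Simulated, 25 per arm | Simulated, 30 per arm |
|---|---|---|---|---|
| 0.1 | 1.3 | 8.6% | not run | not run |
| 0.3 | 1.9 | 15.5% | 15.2% | 16.0% |
| 0.5 | 2.5 | 21.5% | 21.0% | 21.2% |
| 0.7 | 3.1 | 26.6% | 26.9% | 26.5% |
| 0.9 | 3.7 | 30.8% | not run | not run |

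The simulations fitted the ANCOVA on group, visit and age with no true group effect, 5,000 runs per setting. At ICC 0 they gave 4.8% and 4.9%, as they should. If only a pre/post pair of scans were pooled, the design effect would be 1 + ICC and the error 8.6% to 13.3% for ICC 0.3 to 0.7.

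**Step 3: which omission does what.** In the same simulations an ANCOVA on participant means, which has a between-participant error term, gave 4.5% to 5.1%. The missing participant term is therefore the cause of the inflation. Adding group-by-visit without a participant term does not repair the model. That interaction test rejected in 0% to 1.4% of runs at ICC 0.3 to 0.7, which is too conservative.

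**Step 4: the three descriptions side by side.**

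| Place | Comparison | Uses visit 1 as reference? | Respects repeated scans? |
|---|---|---|---|
| 2.6.2 | Change from pre- to post-training, between arms | Yes | Yes, a within-participant change |
| 2.10, opening | Group and time, mixed-model ANOVA | Yes, if the interaction is the test of interest | Yes |
| 2.10, fMRI paragraph | Group, adjusted for visit and age | No | No, read literally |

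They test different hypotheses with different error terms.

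**The case against.** The best defence is that the protocol already contains sound fMRI tests. The change-score comparison in 2.6.2 uses the pre-training scan as reference, and the mixed-model ANOVA handles repeated measures. The main fMRI measures (ROI amplitude, volume and laterality index) are naturally read as extracted imaging parameters, so the ANOVA may be meant for them and the ANCOVA only for whole-brain maps. A one-sentence list of covariates in a condensed article does not prove that a participant term is absent, and regressors and contrasts are left to a cited study.

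Much of this stands. A reader might infer that the authors have declared the scans independent, or that no valid fMRI test is planned. The documents say neither: independence follows only from a literal reading of the listed terms, and two of the three descriptions respect the repeated measures.

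The objection does not remove the point. The ANCOVA is the sentence that assigns a test to fMRI group effects, and nothing confines it to whole-brain maps or ranks it below the other two. If it does apply only to maps, averaging the pre-training scan into the group effect is still the wrong contrast there. The cited study is followed only in part, and deferring to it does not settle the conflict between 2.6.2 and 2.10.

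**Conclusion.** The sentence is wrong as written and should be changed. The group term mixes pre- and post-training scans and does not test differential change. An equal effect at visits 2 to 4 would be reported at 75% of its size. This part does not depend on the ICC. The conflict among the three descriptions is plain on the page.

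The error rate is conditional. It is about 15-27% at an assumed ICC of 0.3-0.7 (about 9-31% at 0.1-0.9), if all four scans are pooled without a participant term and tested at two-sided 5%. A reader might take 15-27% as the trial's actual false-positive rate, or blame the missing interaction for it. The first is unsupported because the documents give neither an ICC nor an alpha for fMRI. The second is wrong because only the missing participant term inflates the error.

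The point concerns a secondary outcome measured in half of the participants. The analysis of gait speed is not affected.

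**What to change.** Replace the ANCOVA sentence in 2.10 with one model, and use the same definition in 2.6.2.

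- **ROI measures:** a mixed model with a participant effect and age. Define the fMRI group effect either as the group-by-visit contrast or as the post-training between-arm contrast adjusted for the visit 1 value.
- **Voxel-wise maps:** form the within-participant change first, then compare arms at the second level.
- **Precedence:** state that the general mixed-model ANOVA and its non-parametric fallback do not serve as a second test of the same fMRI group effect. Fix this before the interim data are seen.

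Both parts are needed: a participant effect alone leaves the wrong contrast, and an interaction alone leaves the wrong error term. The cost is wording only, with no new data. The downside is that, at ICCs of 0.3 to 0.7, standard errors will be wider than those the literal ANCOVA would report, so fewer imaging results will be called significant.
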